### Sample size {14}

The primary outcome is the change in TUG time between pre- and post-intervention evaluations. The power of the study was set at 80%, with a significance level (α) of 5%. The clinically significant effect size (δ) was determined to be 4.9, and the expected standard deviation (σ) is estimated to be 4.0 [48, 49]. The analysis was conducted using Lehr’s formula, resulting in a required sample size of 10.6 [50].$$\text {Lehr's}\,\mathrm{formula}=\left(16/(\delta/\sigma)\right)=\left(16/(4.9/4.0)\right)^2=10.6$$

The follow-up rate was targeted at 75%, based on the conventional outpatient rehabilitation treatment criteria over a 4-week period. Therefore, the sample size for each sub-study was determined to be 30.

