## Statistical methods

### Statistical methods for primary and secondary outcomes {20a}

Demographic data are presented as means and standard deviations for continuous variables, while frequencies and percentages are used for categorical variables. Efficacy analysis are based on the assessment of the change from pre-intervention evaluation within each sub-study. To compare the baseline characteristics between the experimental and control groups in each sub-study, Student’s *t*-test for normally distributed variables or the Wilcoxon singed-rank test for non-normally distributed variables is employed. The Shapiro–Wilk test is used to examine the normal distribution of the variables.

To evaluate the effects of time, group, and the interaction of time with the group, we employ repeated-measures analysis of variance and repeated-measures analysis of covariance for variables exhibiting a normal distribution. Non-parametric variables are analyzed using a generalized estimating equation. Statistical significance is set at *P* < 0.05. A comparison between the sub-studies is not considered.

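### A normality pre-test chooses the efficacy method and sends non-normal outcomes to GEE, which is not non-parametric and is fragile at 22–30 patients per sub-study; the switch gives no benefit and costs some error control

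*Protocol article*

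**What the plan says.** In the protocol article, section {20a}, efficacy is analysed as change from the pre-intervention evaluation, separately within each sub-study. "The Shapiro–Wilk test is used to examine the normal distribution of the variables". Variables that look normal go to repeated-measures ANOVA and ANCOVA for time, group and their interaction. For the others, "Non-parametric variables are analyzed using a generalized estimating equation". "Statistical significance is set at" P < 0.05. The section gives no link, working correlation, variance estimator or reference distribution for the GEE.

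Sections {12} and {14} define the primary outcome as the change in TUG time from pre- to post-intervention. Section {14} also fixes the scale: "the sample size for each sub-study was determined to be 30", with 75% follow-up targeted. Section {16a} allocates 1:1 within each sub-study, and {20a} rules out comparing the sub-studies, so each is analysed alone.

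**The concern.** Three features of the stated rule cause trouble.

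- The method for the primary outcome is decided by a preliminary test on the trial's own data. The analysis is therefore not fixed until the data are seen. The text speaks of testing variables and does not say whether these are raw values, changes or model residuals.
- GEE is a semi-parametric model for means. With an identity link it targets the same mean difference as the ANOVA it replaces. It is neither rank-based nor distribution-free, so calling the diverted outcomes non-parametric misdescribes what the fallback does.
- The standard GEE variance is justified when there are many independent subjects. With 22–30 it tends to be too small, and the Wald test then rejects too often.

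At stake is whether the stated 5% level holds for outcomes that take the fallback. TUG times are bounded below and may be right-skewed, so the primary outcome could be one of them.

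**Working it through.** **Patients per analysis.** Section {14} states: "The clinically significant effect size (δ) was determined to be 4.9"; "the expected standard deviation (σ) is estimated to be 4.0"; "resulting in a required sample size of 10.6". Lehr's rule gives 16/(4.9/4.0)² = 10.66, which reproduces that figure and rounds up to 11 per arm. (As printed, the expression squares the whole fraction and would give 170.6; this does not affect the present point.) Allowing for 75% follow-up, 11/0.75 = 14.7, so 15 per arm and 30 per sub-study. The GEE would therefore rest on about 22 (11 per arm) to 30 (15 per arm) patients.

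**Error on the GEE branch, closed form.** Assume normal data, a saturated group-by-time model with identity link, n per arm, and an uncorrected sandwich variance with a chi-square reference. The robust Wald statistic is then Hotelling's T² × n/(n−1). With ν = 2n−2 and p degrees of freedom,

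error = P{ F(p, ν−p+1) > χ²₀.₉₅,ₚ × (n−1)/n × (ν−p+1)/(pν) }.

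| n per arm | p | F threshold | Error at nominal 5% |
|---|---|---|---|
| 11 | 1 | 3.841 × 10/11 = 3.49 on (1, 20) df | 7.6% |
| 11 | 2 | 5.991 × 10/11 × 19/40 = 2.59 on (2, 19) df | 10.2% |
| 11 | 3 | 7.815 × 10/11 × 18/60 = 2.13 on (3, 18) df | 13.2% |
| 15 | 1 | 3.841 × 14/15 = 3.59 on (1, 28) df | 6.9% |
| 15 | 2 | 5.991 × 14/15 × 27/56 = 2.70 on (2, 27) df | 8.6% |
| 15 | 3 | 7.815 × 14/15 × 26/84 = 2.26 on (3, 26) df | 10.5% |

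The primary pre-to-post contrast is the p = 1 case. The p = 3 case is a joint time-by-group test over the four TUG visits.

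**Simulation check.** There were 40,000 null trials per setting, with normal or lognormal data (log-SD 0.5 or 0.8) and correlation 0.5 or 0.8. The distributions and correlations are assumptions; the protocol gives neither.

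- GEE, 1 df: 6.6–7.8% with 11 per arm, 6.0–7.1% with 15.
- GEE, 3 df over four visits: 11.1–13.3% with 11 per arm, 8.7–10.6% with 15.
- Repeated-measures ANOVA interaction on the same data: 3.8–5.1%, skewed data included.
- t-test on change: 3.9–5.2%, skewed data included.

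The inflation appears with normal data too, so it comes from the small number of patients, not from skewness.

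**The whole two-step rule.** Here the gate is applied first, and the GEE is used only when Shapiro–Wilk rejects.

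- Normal data, gate on baseline values: about 5% of trials are diverted, and overall error is 5.1–5.6%.
- Lognormal data with log-SD 0.5 or 0.8, gate on baseline values, correlation 0.7: overall error is 5.9–6.4% at two visits and 8.2–10.3% for the joint test at four visits.
- Lognormal TUG with CV 0.25–0.5, primary contrast: Shapiro–Wilk rejects in roughly 20–68% of samples when raw values are tested, but in only about 9–33% when changes are tested. Across checks, overall error is about 5–7%.

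**Other GEE variances.** A Mancl–DeRouen type correction gave 4.3–5.3% at two visits but still 5.7–8.6% for the 3-df test with a chi-square reference. Model-based standard errors, in a smaller check with skewed data, gave 4.7–5.1% at four visits but 9.6–11.8% at two.

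**The case against.** The strongest reply is that the inflation belongs to an estimator the protocol never names. A statistical analysis plan that is not shown could specify a small-sample correction, and leaving that detail to it is normal. This stands: every GEE error rate above is conditional on the uncorrected sandwich with a z or chi-square reference.

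A reader might also infer that the primary test as planned rejects a true null well above 5%. The documents do not support that. The double-digit figures belong mainly to the joint 3-df test, which the section evaluates but does not name as primary. The primary outcome is a 1-df contrast, and only some trials would reach the GEE. If the gate is applied to changes, which are more symmetric than raw times, fewer still would.

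Three smaller points also stand. GEE does not assume normality and could be run with a log link or another variance function, so it would be too strong to say that it cannot accommodate skewness; the protocol simply specifies no such form. The Shapiro–Wilk sentence sits beside the baseline comparisons, so what exactly is tested is partly inference. The trial is described as exploratory, which limits the consequence of an excess of a point or so. Against that, section {14} sets power and α, and section {6b} presents the comparator as the means of showing superiority, so error control is not irrelevant.

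None of this answers the first two features of the rule: the method depends on the data, and the fallback is not what it is called.

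**Conclusion.** The point holds in a limited form. The written rule lets a normality test choose the efficacy method, the primary TUG change included. It then sends non-normal outcomes to a mean-based, large-sample method in sub-studies of about 22–30 evaluable patients.

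Under an uncorrected sandwich variance with a z or chi-square reference, the GEE branch runs at about 7–8% for the primary contrast and about 10–13% for the joint four-visit test. Some skewed settings fall slightly lower, to 6.0% and 8.7%. Over both steps the primary contrast is at about 5–7% under assumed lognormal TUG, and close to 5% if TUG is normal.

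The loss for the primary result is therefore modest. It is also unnecessary: t-based tests of the change stayed at 3.9–5.2% on the same data, so the gate swaps a test that keeps its level for one that may not. The case for changing the rule rests mainly on pre-specification and on the wrong choice of fallback. The numbers support it but do not show a seriously inflated primary test.

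**What to change.** Remove the normality gate from section {20a} and name one primary model for post-intervention TUG within each sub-study: ANCOVA adjusted for baseline TUG, or a mixed model with Kenward–Roger inference and the pre-to-post group contrast stated explicitly. List two sensitivity analyses in advance: the same model on log-TUG, and a permutation test of the same contrast that follows the randomisation scheme.

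If GEE is kept for any outcome, state the link and working correlation, and require a small-sample variance correction (for example Mancl–DeRouen or Kauermann–Carroll) together with a t or F reference. The correction alone was not enough for the multi-df test. Drop the term non-parametric for these variables.

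The cost is a wording change in the protocol or analysis plan, dated before allocation is revealed to the analysts, and trivial programming. No patients, visits or measurements are added.

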### Interim analyses {21b}

Not applicable. No formal interim analysis has been planned.

### Methods for additional analyses (e.g., subgroup analyses) {20b}

Not applicable. No subgroup analysis has been planned.

### Methods in analysis to handle protocol non-adherence and any statistical methods to handle missing data {20c}

All participants involved in this study and those undergoing intervention are included in the intention-to-treat (ITT) set. Safety analyses are conducted based on the ITT dataset. Participants in the ITT set who undergo the TUG test at both pre- and post-intervention evaluations are categorized as the full analysis set (FAS). Efficacy analysis will be based on the FAS. Those in the ITT set who successfully complete the study with no significant protocol violations are classified into the per-protocol (PP) set. Efficacy analyses within the PP set are conducted alongside the FAS. In the event of disparities between the FAS and PP analyses, the reasons behind such difference will be investigated. For missing values, data will be analyzed using the last-observation-carried-forward method, assuming that the most recent observation was obtained at that time point.

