### Criteria for discontinuing or modifying allocated interventions {11b}

The criteria for discontinuing the intervention are as follows:Voluntary discontinuation by the participant: Participants have the freedom to withdraw from the trial at any time without providing an explanation, and this will not affect their future treatment.Missed follow-up visits.Discontinuation due to a significant adverse event or if the participant or legal representative requests termination due to adverse events.Based on the investigator’s judgment, the progression of a clinical trial may be deemed unsuitable.Significant protocol violation or deviation from inclusion/exclusion criteria during the clinical trial.Study adherence < 80%.$$\text{Adherence }\left({\%}\right)= \left(\frac{\text{Actual number of rTMS sessions performed}}{\text{Total required rTMS sessions}}\right)\times 100$$

Modifications of allocated interventions are not considered.

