### Procedure for unblinding if needed {17b}

This is a single-blind study; therefore, the assessors and participants will not be informed of the study arm. However, unblinding should be considered in cases of serious medical emergencies. In the event of a serious medical emergency, unblinding will be performed only if information regarding the stimulation protocol affects the participant’s treatment. Unblinded participants will not be permitted to continue within the study.

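### Efficacy is analysed only in participants who have the post-intervention TUG, so the primary analysis is complete-case, LOCF fills nothing there, and at 2 months LOCF assumes the effect has lasted

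*Protocol article*

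**What the plan says.** All of the analysis-set rules are in section 20c of the protocol article.

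- The full analysis set (FAS): "Participants in the ITT set who undergo the TUG test at both pre- and post-intervention evaluations are categorized as the full analysis set (FAS").
- Its use: "Efficacy analysis will be based on the FAS". The ITT set is assigned to safety only.
- The second efficacy set: "Those in the ITT set who successfully complete the study with no significant protocol violations are classified into the per-protocol (PP) set".
- The only missing-data rule: "For missing values, data will be analyzed using the last-observation-carried-forward method".

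Other sections bear on this:

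- Outcomes (12) makes the pre-to-post change in TUG time primary and the 2-month TUG secondary. The post visit falls within 48 h of the last session. Outcomes and Table 2 also schedule a TUG at the mid-intervention visit.
- Sample size (14): "The follow-up rate was targeted at 75" per cent, tied to a 4-week period.
- Section 11b lists the reasons for stopping the intervention, among them adverse events, missed visits, investigator judgement, protocol violation, and "Study adherence < 80" per cent.
- Section 17b: "Unblinded participants will not be permitted to continue within the study".

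**The concern.** A set that admits only participants with the primary outcome measured is a complete-case set, whatever it is called. Randomisation protects the comparison of everyone randomised; it does not protect a comparison of those who reached the post visit. The reasons for leaving that the article lists all arise after randomisation and could relate to arm or to response.

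The rule is stricter than the familiar exclusion of patients with no data after baseline. Here a participant with a mid-intervention TUG but no post TUG is removed, and that measurement goes unused. The per-protocol analysis gives no cross-check, because it too contains completers only.

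LOCF has a separate weakness at the 2-month visit. Copying the immediate post value forward assumes the persistence that the visit is there to test.

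**Working it through.** **1. The plan's own figure.** Inputs from Sample size (14): effect 4.9 and SD 4.0 (taken as seconds), 80% power, α 5%, follow-up 75%.
- Lehr's formula: 16/(4.9/4.0)² = 10.66 per arm; the article gives 10.6. The printed equation has its exponent misplaced and would evaluate to 170.6, but the stated result is right.
- Inflation: 11/0.75 = 14.7, so 15 per arm and 30 per sub-study. The stated size reproduces.

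**2. Expected exclusions.** 30 × 0.25 = 7.5, so 7 or 8 per sub-study, leaving about 11 of 15 per arm. The 4-week period is the span from baseline to the primary visit, so this loss falls before or at the visit that defines the FAS. Power by t-test is 0.78 with 11 per arm and 0.90 with 15 (normal approximation 0.82 and 0.92). The loss is budgeted for power, but a larger N does not remove selection.

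**3. What LOCF does for the primary endpoint.** Every FAS member has both TUG values by definition, and every per-protocol member has completed the study. The number of primary values filled is 0 in both sets.

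**4. Size of complete-case bias.** Let f be the share lost in an arm and g the amount by which completers improve more than dropouts. Then bias in the arm difference = f_E·g_E − f_C·g_C.
- 25% lost in each arm and equal g: 0.
- 35% lost in the experimental arm, 15% in control, g = 2 in both: 0.35×2 − 0.15×2 = 0.4 s. With g = 4: 0.8 s. With the loss rates swapped, the sign reverses.

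A simulation gives a similar picture. Assumptions, none of them from the article: no true effect, SD of change 4 s, correlation 0.7 between mid and post change, and dropout depending on being more than 2 s worse at the mid visit.

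| Experimental dropout (worse / others) | Control dropout | False benefit in FAS |
|---|---|---|
| 0.70 / 0.08 | same rule | about 0 s |
| 0.40 / 0.18 | 0.25 at random | about 0.3 s |
| 0.70 / 0.08 | 0.25 at random | about 0.8 s |

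In the last row overall dropout is nearly equal (27% against 25%), so similar dropout counts would not rule the bias out. A model using the mid-visit TUG returns about 0.0 s in that row. It does so by construction, because dropout was made to depend on the mid value alone.

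**5. LOCF at 2 months.** Let m be the share of the FAS missing the 2-month TUG and r the share of a 4.9 s post effect still present then. The true effect is 4.9r, and LOCF estimates 4.9[r(1 − m) + m]. The overstatement is 4.9·m·(1 − r). The article gives neither m nor r.

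| m | r = 0 | r = 0.5 | r = 1 |
|---|---|---|---|
| 5% | 0.25 s | 0.12 s | 0 |
| 10% | 0.49 s | 0.25 s | 0 |
| 20% | 0.98 s | 0.49 s | 0 |

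**The case against.** The strongest reply is that bias needs missingness to relate to outcome differently in the two arms, and nothing in the article shows that it will. Both arms receive active rTMS, participants and assessors are blinded, expectations are set alike for all, and the visit schedules are identical. The trial is expressly exploratory, the loss is allowed for in N, and 75% is a target rather than a forecast. All of this stands, and it is why the bias is given as a range that includes zero. It does not rescue the set definition: no planned efficacy analysis could show that the bias is absent.

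Four stronger readings are tempting, and the article does not support them.

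- A reader might infer that the randomised comparison is broken and the 2-month result biased. Both are conditional: the first on dropout that differs by arm in its relation to outcome, the second on the effect waning or missingness differing by arm.
- A reader might apply the 25% loss to the 2-month visit and get 0.25 × 4.9 = 1.2 s of false persistence. That counts the same patients twice. The 25% belongs to the first 4 weeks, and those patients have already left the FAS. Only further loss after the post visit can be carried forward to 2 months.
- A reader might say that LOCF contradicts the FAS. It is redundant for the primary endpoint, but it can still fill mid-intervention, 2-month and other secondary values.
- A reader might assume that anyone meeting a criterion in section 11b leaves the FAS. That section concerns stopping the intervention. As section 20c is worded, a participant with low adherence who has a post TUG stays in the FAS.

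Sensitivity-analysis detail may well be in an unseen analysis plan. The set definition and the LOCF rule, however, are stated in the article.

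**Conclusion.** The point holds as a criticism of two stated rules. The primary analysis is complete-case by definition, and up to 7 or 8 of 30 per sub-study could be excluded at the planning allowance. The FAS and per-protocol comparison cannot detect the consequence. The bias is zero when dropout relates to outcome equally in both arms and was about 0.3 to 0.8 s in the assumed one-sided scenarios, against a target effect of 4.9 s; its direction would reverse if the outcome-related dropout were in the control arm. LOCF does nothing for the primary endpoint. At 2 months it overstates persistence by 4.9·m·(1 − r) s, which is 0.25 to 0.98 s for m = 5 to 20% with the effect gone, and zero if it persists. Those values of m and r are assumptions. The sample size itself is not in question.

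**What to change.** 1. Define the primary efficacy set as all randomised participants with a baseline TUG, analysed as randomised, within each sub-study.
2. Analyse TUG time with a likelihood-based mixed model on the mid-intervention, post and 2-month values, with baseline included. Take the arm contrast at post as primary and at 2 months as secondary.
3. Replace LOCF with this model. Keep the present FAS and per-protocol analyses as supportive.
4. Add a simple sensitivity analysis for non-random missingness, for example a delta adjustment, since the mixed model relies on missingness being explained by the observed values.
5. State that the already scheduled post and 2-month TUG is still collected from participants who stop sessions, unless they withdraw consent. Reconcile this with sections 11b and 17b, which leave open whether outcome visits continue after the intervention stops or after unblinding. This concerns data collection only, not treatment.

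The cost is protocol wording, slightly more modelling, and keeping visits that are already scheduled. N stays at 30 per sub-study. Item 5 needs settling while visits are still being held, because a TUG that was not taken cannot be recovered.

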### Outcomes {12}

Pre-intervention evaluations will be conducted within 3 days before the initial intervention session. Post-intervention evaluations will be conducted within 48 h after the final intervention session. Follow-up evaluations will be conducted 2 months after the intervention concludes. The primary outcome is the difference in TUG time between the pre- and post-intervention evaluations. Secondary outcome variables include the TUG measured at follow-up evaluations. Additionally, the TUG-Cog, MDS-UPDRS Part III, New Freezing of Gait Questionnaire (NFoGQ), Digit Span, trail-making test, transcranial magnetic stimulation-induced motor-evoked potential (TMS-induced MEP), diffusion tensor imaging (DTI), and rsfMRI are assessed pre-intervention, post-intervention, and at follow-up to investigate the effectiveness of personalized rTMS.

The TUG assesses ambulatory functions, including gait, balance, mobility, and fall risk. In the TUG, the participants are instructed to rise from a chair, walk to a traffic cone located 3 m away at a comfortable pace, return to the chair, and sit down. The TUG-Cog involves the simultaneous execution of the TUG test and serial subtraction in three, starting from a randomly selected number between 80 and 100 [34]. The TUG-Cog is designed to provide a comprehensive assessment by incorporating both motor and cognitive tasks. The TUG and TUG-Cog are each measured twice, and the mean values are utilized for analysis. During the TUG and TUG-Cog, the participants wore shoes equipped with a smart insole (Gilon Gait Data Collector & Analyze MD, Gilon Inc., Gyeonggi, Republic of Korea). The smart insole measures gait parameters including stride length, step count, cadence, velocity, distance, swing ratio, and foot plantar pressure (heel/mid/toe). The stride lengths of the TUG and TUG-Cog are utilized to assign sub-studies and evaluate the efficacy of the intervention. During the mid-intervention evaluation, the TUG is conducted without smart insoles.

The MDS-UPDRS part III assesses the motor symptoms of PD using 18 items, with each item scored on a scale of 0 to 4 [46]. Higher scores indicate more severe symptoms. The NFoGQ consists of nine items designed to assess the severity of freezing of gait (FoG) and gait disturbance [47]. The NFoGQ has demonstrated reliability in measuring both the severity of FoG and its functional impact in patients with PD.

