### Participant timeline {13}

Figure 1 presents a comprehensive flowchart of the study process, including the allocation phase. After enrollment and screening, a pre-intervention evaluation is conducted. Based on the pre-intervention evaluation, participants are classified into sub-studies and allocated to either the experimental or control group. The first rTMS session takes place within 3 days of the pre-intervention evaluation. The initial 5 interventions are administered within 2 weeks, with a mid-intervention evaluation employed within 24 h following the fifth session. Subsequently, an additional 5 rTMS sessions are administered over the next 2 weeks, and within 48 h of completing all intervention sessions, an immediate post-intervention evaluation is conducted. Follow-up evaluation is performed 2 months after the completion of the intervention, marking the end of the study. The total study duration is anticipated to be approximately 12–14 weeks. The timelines for both the experimental and control groups in the sub-studies are identical (Table 2).

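### The per-protocol set is tied to the 2-month visit, so its supporting analysis of the 4-week primary endpoint can lose participants who were treated and measured as planned

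*Protocol article*

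**What the plan says.** All references are to the protocol article.

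- **PP set** (section 20c): "Those in the ITT set who successfully complete the study with no significant protocol violations are classified into the per-protocol (PP) set". PP efficacy analyses are run beside the FAS analyses, and the reasons for any disparity are to be looked into.
- **End of study** (Participant timeline, section 13): "Follow-up evaluation is performed 2 months after the completion of the intervention, marking the end of the study". Table 2 labels the same visit as close-out.
- **Primary outcome** (Outcomes, section 12): "The primary outcome is the difference in TUG time between the pre- and post-intervention evaluations". On timing: "Post-intervention evaluations will be conducted within 48 h after the final intervention session".
- **2-month TUG** (section 12): "Secondary outcome variables include the TUG measured at follow-up evaluations".
- **FAS** (section 20c): membership needs a TUG at the pre- and post-intervention evaluations and nothing later. "Efficacy analysis will be based on the FAS".
- **Discontinuation criteria** (section 11b): these include adherence below 80% of the required sessions and, as a separate item, "Missed follow-up visits".

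**The concern.** A PP analysis of the primary endpoint should show what happens among participants who were treated and measured as the protocol intended, up to the time of that endpoint. Here, entry to the set also depends on attending a visit two months after the endpoint was recorded. Whether someone returns may be related to perceived benefit or to adverse effects, and it may differ between arms, so selection on it can disturb the randomised comparison within the PP set.

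What is at stake is how the FAS and PP results are compared. The protocol promises to investigate disparities between them. With this definition, a disparity can arise from non-adherence, from protocol violations, or from later retention that has no bearing on how the 4-week TUG was obtained. The PP analysis would also lose some primary-endpoint data in a sub-study of only 30 participants.

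**Working it through.** **1. Reading the sections together.** Take a participant with 10 of 10 sessions, a pre-intervention TUG, a post-intervention TUG within 48 h of session 10, no violation, and no 2-month visit.

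| Set | Requirement in the article | This participant |
|---|---|---|
| FAS | TUG before and after the intervention | In |
| PP | Study completed, no significant violation; study ends at 2 months | Out |

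Nothing in the article limits study completion to the treatment course or to the post-intervention visit. The FAS definition in the same section is tied to the pre- and post-intervention TUG; the PP definition is not.

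**2. The plan's sample size.** Inputs from section 14: difference 4.9, standard deviation 4.0, power 80%, alpha 5%, follow-up 75%. Section 16a gives 1:1 allocation.

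- Lehr's formula: 16 / (4.9/4.0)² = 16 / 1.5006 = 10.66 per arm. This agrees with the stated 10.6. (As printed, the square sits outside the whole bracket, which would give about 170.6; this does not bear on the present point.)
- Rounded up to 11 per arm: 11 / 0.75 = 14.7, so 15 per arm and 30 per sub-study, as stated.

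The 75% is described as applying to a 4-week period. Loss between week 4 and month 2 is not part of the calculation.

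**3. Size of the PP set for the primary endpoint.** Let m be the share of participants with a 4-week TUG who miss the 2-month visit. The article gives no value, so m is assumed. Exclusions for adherence or violations are ignored here.

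Expected PP size per arm = 15 × 0.75 × (1 − m). From sample size alone, the confidence interval widens by the factor √(1/(1 − m)).

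| m (assumed) | PP per arm | Interval width relative to m = 0 |
|---|---|---|
| 0 | 11.25 | 1.00 |
| 10% | 10.1 | √(1/0.9) = 1.05 |
| 20% | 9.0 | √(1/0.8) = 1.12 |

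With the protocol's own difference and standard deviation, and a normal approximation, power in the PP set would be 82.8%, 78.7% and 73.8% in these three rows. This is for scale only, since the article does not say that the trial is powered on the PP set.

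**The case against.** **The article is condensed.** Operational PP criteria are often settled in the full protocol or the analysis plan, and the timeline sentence was not written to define an analysis set. Those documents may well narrow the phrase. But the article is not silent: it states a membership rule and it states when the study ends, and together they give the result above.

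**One completers' set for all outcomes is coherent.** The efficacy models are repeated-measures analyses and several outcomes are taken at 2 months. That supports requiring the 2-month visit for 2-month outcomes. It does not support requiring it for an endpoint defined as pre to post. Section 20c also already has a last-observation-carried-forward rule for missing values, so a missing 2-month value need not exclude anyone.

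**Stronger readings that the article does not support.**
- A reader might infer that the main result loses valid data. It does not: efficacy is based on the FAS, which keeps these participants.
- A reader might infer that the PP set ignores adherence, so that the FAS/PP comparison is useless. Section 11b makes adherence below 80% a discontinuation criterion, and a discontinued participant can hardly be said to have completed the study. Adherence therefore screens PP membership indirectly, and significant violations are excluded by name. The comparison is blurred, not void, and the promised inquiry into disparities could bring 2-month losses to light.
- A reader might take "Missed follow-up visits" to mean the 2-month visit, which would make it a reason to stop an intervention that has already ended. The wording is ambiguous: section 14 uses the term follow-up for the 4-week period too, so the item may mean any scheduled visit. It calls for clarification and does not establish a contradiction.

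**Conclusion.** The point holds for the supporting PP analysis only. On the text shown, a participant treated and measured as planned for the primary endpoint is removed from that analysis for missing a visit two months later. PP membership then depends partly on post-endpoint retention, and a FAS/PP disparity cannot be read as the effect of adherence and violations alone.

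Under an assumed later loss of 10% to 20%, the PP set shrinks from about 11 to about 10 to 9 per arm and its interval widens by about 5% to 12%. These figures also assume that the 75% target is met exactly and equally in both arms. They count every participant lost at 2 months as otherwise eligible for the PP set; some may have violations that would exclude them anyway, so the loss due to this rule alone could be smaller. The selection problem does not depend on these figures. The primary FAS result is unchanged.

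**What to change.** In section 20c, define the PP set for the primary endpoint by events up to the post-intervention evaluation: the protocol's existing adherence threshold met, pre- and post-intervention TUG done, and no significant violation by that time. Require the 2-month evaluation only for PP analyses of 2-month outcomes. Stating the adherence threshold in the PP definition itself would make explicit what now acts only through the discontinuation criteria.

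Separately, reconcile sections 11b, 12 and 13 on which visits "Missed follow-up visits" refers to. This review takes no position on what that criterion should be.

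The cost is wording only, with no added data, visits or participants. The change should be made and dated before the allocation is revealed.
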